## Correlation between PET data and Blood and Tissue markers

The correlation between the continuous variable SUV and the categorical variables tissue PD-1 and PD-L1 IHC will be assessed with the ANOVA test. The correlation between the continuous variable SUV and the categorical blood variables will be assessed with the T test.

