### PET imaging

PET imaging using biological active tracers could represent a valuable method to identify suitable biomarkers for personalized (immuno)therapy. The advantage of PET over IHC is the possibility to visualize tracer distribution in the entire body to appreciate heterogeneity, and to repeat imaging during the course of treatment/disease to investigate changes over time [37].

Recently, PD-1 and PD-L1 expression has been imaged at VUmc in patients with NSCLC with ^89^Zr labeled nivolumab (PD-1) and [^18^F]BMS-986192 (PD-L1 ) PET, respectively [38]. In all 7 patients tumor uptake was visualized for both tracers in all patients. For lesions with < 50% PD-L1 IHC, [^18^F]BMS-986192 PET showed moderate uptake (SUV 3.4 (±2.9)) compared to lesions with ≥50% PD-L1 IHC (SUV 7.1 (±6.0); p = 0.22). These data demonstrated the feasibility to show inter- and intra-patient heterogeneity with [^18^F]BMS-986192, supporting its further development as a potential biomarker for response to nivolumab.

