### [18F]BMS-986192 PET

Selecting those patients that benefit the most from nivolumab treatment is challenging. As discussed above, until now companion biomarker development has focused on the level of PD-L1 expression by IHC. [18F]BMS-986192 PET in NSCLC has shown non-invasive quantification of the PD-L1 receptor in tumors [38], so far the most frequently used (ex-vivo) tissue biomarker for patient selection in current trials with anti-PD-(L)1 mAbs. With [18F]BMS-986192 PET it will be possible to visualize and quantify in vivo PD-L1 IHC and provide unique comparative insight in the relative performance of tumor tissue PD-L1 IHC. A tumor biopsy providing tissue for PD-L1 IHC shows the level of expression for a small part of one tumor lesion. Whether this is representative for other parts of that lesion or for other tumor lesions is not known and might influence the predictive value of PD-L1 IHC. Because the PET technique is non-invasive and whole body, it allows to quantify whole tumor uptake as well as looking at heterogeneity within and between tumor lesions, changes over time during treatment and uptake at immunomodulatory locations such as tumor-draining lymph nodes (TDLN).

We hypothesize that [^18^F]BMS-986192 tumor uptake will differ between tumor lesions (primary tumor and affected lymph nodes) and patients and that the uptake is correlated with PD-L1 expression and response to nivolumab treatment. In addition, we hypothesize that expression level of PD-L1 will change during treatment with nivolumab. Quantitative [^18^F]BMS-986192 PET might elucidate spatial and temporal heterogeneity and changes in expression in patients with locally advanced oral cancer before and on treatment with nivolumab.

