## Sample size calculation

Since this is a pilot feasibility study to investigate safety and tolerability, [^18^F]BMS-986192 and [^18^F]-FDG PET imaging before and on treatment with nivolumab, a sample size of 15 evaluable patients has been chosen. The objective of this study is descriptive and hypothesis generating, so no formal statistical justification for the sample size is provided.

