## Secondary study parameters/endpoints

#### Heterogeneity analysis

#### Interpatient, intrapatient and intratumor SUV heterogeneity.

Correlation between both PET scans, and between imaging and response

The correlation between SUV for [^18^F]BMS-986192 and [^18^F]-FDG baseline and on treatment and early response evaluation with [^18^F]-FDG.

Correlation between PET data and Blood/Tissue markers

The correlation between continuous values as SUV and the categorical variables tissue PD-1 and PD-L1 IHC will be assessed for each tumor lesion. Correlation with immuno-monitoring analysis in tumor tissue/lymph nodes and blood, plasma vesicle miRNAs from blood, as well as DNA/RNA profiling in tumor tissue at baseline and at surgery will be assessed.

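### Section 9.4 tests an ordered SUV–PD-L1 question with an unordered ANOVA, which gives no correlation estimate and usually has less power than a rank or trend analysis

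*Protocol*

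**What the plan says.** Section 9.4 fixes the method for relating tracer uptake to tissue: "The correlation between the continuous variable SUV and the categorical variables tissue PD-1 and PD-L1 IHC will be assessed with the ANOVA test". The next sentence of that section assigns a t-test to the blood variables. Neither sentence names a transformation, a rank method or a trend test, and the protocol does not give the number or cut-offs of the IHC categories.

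Section 6.2 lists this among the secondary endpoints and sets the unit of analysis: "The correlation between continuous values as SUV and the categorical variables tissue PD-1 and PD-L1 IHC will be assessed for each tumor lesion".

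Section 1.2.1 gives the hypothesis for the PD-L1 tracer, that "the uptake is correlated with PD-L1 expression and response to nivolumab treatment". The only uptake figures by PD-L1 group are in section 1.1.4, from 7 patients with non-small cell lung cancer. Lesions below 50% PD-L1 had "SUV 3.4 (±2.9)) compared to lesions with ≥50% PD-L1 IHC (SUV 7.1 (±6.0); p = 0.22".

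On size, section 4.3 says "a sample size of 15 evaluable patients has been chosen", calls the study descriptive and hypothesis generating, "so no formal statistical justification for the sample size is provided".

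**The concern.** The hypothesis is directional: uptake should be higher where PD-L1 expression is higher. PD-L1 IHC is an ordered score; section 1.1.3 describes it by levels of 1%, 5% and 10%. One-way ANOVA asks only whether the category means are all equal. Shuffling the category labels leaves its result unchanged, and it gives no coefficient that says how closely uptake follows expression. What the section says it will assess and what the named test delivers are therefore different things.

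The scale is a second issue. Ordinary ANOVA pools one error variance over all groups. If SUV is right-skewed and its SD grows with its mean, a few high values in the high-expression group inflate that pooled error and hide the difference of interest.

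At stake is how much the tracer-versus-tissue comparison can show in 15 patients. A pilot of this kind should hand a later trial an estimate with its uncertainty, and an omnibus p-value does not do that.

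**Working it through.** **No figure to reproduce.** The protocol states no alpha, power or effect size for this test. The check is therefore a simulation built on the protocol's only relevant data.

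**Spread of SUV (section 1.1.4).**
- SD/mean: 2.9/3.4 = 0.85 and 6.0/7.1 = 0.85. The SD doubles as the mean doubles.
- Mean − 1.96 × SD: 3.4 − 5.7 = −2.3 and 7.1 − 11.8 = −4.7. SUV cannot be negative, so a normal shape does not fit and right skew is implied.
- Log-normal with CV 0.85: log-SD = √ln(1 + 0.85²) = √0.544 = 0.74.

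**Assumptions not in the protocol.** Two-sided 0.05, the number and sizes of the IHC groups, the log-normal shape, and the transfer of the lung cancer spread to oral cancer. Means rise in equal ratios over the pilot range. For three groups the middle mean is √(3.4 × 7.1) = 4.91.

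**Power at n = 15, one lesion per patient.**

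| IHC groups (low to high) | ANOVA, untransformed SUV | Spearman | Linear trend, log SUV |
|---|---|---|---|
| 5/5/5 | 15% | 29–30% | 31–32% |
| 3/3/3/3/3 | 9% | 23% | 24% |
| 2/4/9 | 4% | 23% | 25% |
| 9/4/2 | 27% | 23% | 25% |
| 7/8 (two groups) | 31–32% | 43–44% | 43–44% |
| 10/5 (two groups) | 40% | 39% | 40% |

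For 5/5/5, ANOVA on log SUV has 22%. The step from 15% to 22% comes from the scale, and the step from 22% to about 31% from using the order. With a smaller spread (CV 0.5) the 5/5/5 figures are 40% against 60–63%. With 30 independent lesions (10/10/10, CV 0.85) they are 34% against 56–58%.

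**No association (identical groups, CV 0.85, n = 15).** ANOVA on untransformed SUV rejects 3.7% to 5.2% in ordinary layouts. It rises to 5.9% (2/13) and 6.9% (1/4/10) when a group has only one or two lesions. Spearman rejects 3.9% to 5.5%.

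**Non-monotone pattern (means 3.4/7.1/3.4, 5/5/5).** ANOVA rejects about 23%, Spearman about 3%.

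**Several lesions per patient, no association.** With within-patient correlation 0.8 and 2, 3 or 4 lesions in each of 15 patients, treating lesions as independent gives rejection rates of 9.9%, 17.1% and 24.0% for ANOVA and 11.5%, 17.3% and 23.8% for Spearman. Changing the test does not cure this, so the fix has to deal with it separately.

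**The case against.** The case for leaving section 9.4 alone has real force.

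- **The order argument needs at least three categories.** No cut-offs are given, and the pilot used two groups. Naming ANOVA next to a t-test suggests three or more, but that is inference. With two groups only the scale matters, and the gap is about 12 points in the 7/8 layout and nil in 10/5. This stands as a condition on the size.
- **The gain is not universal.** When few lesions have high expression, ANOVA on untransformed SUV is level or slightly ahead. This stands.
- **Untransformed SUV is an inference** from silence, and an analysis plan could add a transformation. This stands for the scale, but not for the order or the missing coefficient, because ANOVA itself is fixed.
- **The spread comes from 7 patients with another tumour.** Skew is plausible, but a CV of 0.85 in oral cancer remains an assumption.
- **Both approaches are weak at n = 15.** A reader might infer that ANOVA will miss a real correlation that another test would find. The figures do not support that: in the 5/5/5 case the better methods also miss the effect about 70% of the time. A steeper gradient would widen the gap, but the protocol gives no mean below 3.4 to support one.

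A reader might also infer that ANOVA produces false positives. It does not in ordinary layouts. The 23% for the non-monotone pattern is detection of a true difference between categories. The valid remainder is narrower: a significant ANOVA need not support the hypothesis of rising uptake.

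That the study is descriptive lowers the importance, but it argues for an estimate with an interval rather than against one.

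**Conclusion.** The point holds as a mismatch between question and method, with a usual but not universal loss of power. For PD-L1, the ANOVA in section 9.4 ignores the order of the categories and yields no correlation estimate. If run on untransformed SUV, it has about half the power of an ordered analysis in the balanced three-group case (15% against 29–32%) and about 12 points less with two near-equal groups (32% against 44%). There is no gain when high-IHC lesions are few (9/4/2: 27% against 23–25%).

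These sizes rest on log-normal SUV with CV 0.85, one lesion per patient, n = 15, two-sided 0.05 and means rising from 3.4 to 7.1. The type I error of ANOVA is near nominal apart from a modest excess when a group has one or two lesions. For PD-1 the protocol states no direction, so only the scale of SUV is at issue there.

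This is a modest improvement to a secondary analysis in a descriptive pilot, worth making because it costs almost nothing.

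**What to change.** In section 9.4:

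- **PD-L1 IHC:** make the analysis an ordered association, either Spearman's correlation with the IHC score or a linear trend over the ordered categories on log SUV. Report the coefficient with its 95% CI.
- **Lesions:** because section 6.2 works per lesion, use one pre-chosen lesion per patient, or a CI that allows for several lesions per patient, for example a bootstrap that resamples patients. An ordinary Spearman p-value or CI on pooled lesions would not be valid.
- **PD-1 IHC:** keep the comparison across categories, but on log SUV.
- **Description:** keep SUV summaries per IHC category, which also lets a reader see a non-monotone pattern.

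The cost is a sentence or two, with no new data or procedures. The downside is that an ordered analysis has little power for a non-monotone pattern, which the protocol does not hypothesise for PD-L1.

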### Rationale for endpoints

This is a feasibility study of neoadjuvant nivolumab in locally advanced oral cancer combined with [^18^F]BMS-986192 and [^18^F]-FDG PET as well as immuno-monitoring and DNA profiling on tissue and blood in order to identify biomarkers for response and investigate safety.

The primary endpoint of this study is [^18^F]BMS-986192 uptake in tumor lesions and safety and tolerability of neoadjuvant nivolumab. [^18^F]BMS-986192 tumor uptake will be quantified, tumor uptake heterogeneity between patients and within and between tumor lesions of the same patient will be assessed. These results will be correlated with [^18^F]-FDG uptake, as effective treatment with immune therapy may lead to increase in early [^18^F]-FDG uptake, as well as to (pathological) response.

The secondary endpoints include the correlation of the imaging and response data to measured blood and tissue parameters. The immune status will be assessed in the tumor by multiplex immunostaining (see section 3.10.1) and in peripheral blood and TDLN by flowcytometry for the frequency and activation status of immune subsets (see section 3.8). Cytokine profiling may be performed in plasma or from TDLN in ex vivo O/N cultures.

In addition, the presence of neoantigens and the molecular background of the tumor as copy-number-high or copy-number-silent will be determined. Neoantigen analysis will be performed by DNA sequencing using a combined approach of low coverage whole genome sequencing for copy numbers, and exome enrichment sequencing for mutations. Normal DNA from blood will be analyzed in parallel to filter SNPs. In addition RNA sequencing will be performed and the data mined as previously described [53].

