## PET guided additional biopsies

Up to two additional biopsies will be taken when possible with acceptable additional risk in case the PET scan shows heterogeneous and/or discrepant uptake between tumor lesions of the same patient. In this way imaging [^18^F]BMS-986192 PET will aid further validation of PD-L1 IHC.

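### Section 9.4 treats continuous blood markers as undefined categories for a t-test, and compares lesion-level SUV with IHC by an ANOVA with no patient term

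*Protocol*

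**What the plan says.** **Blood.** Section 9.4 says that the correlation between SUV and "the categorical blood variables will be assessed with the T test". Section 1.2.7 describes immune status as measured "in peripheral blood and TDLN by flowcytometry for the frequency and activation status of immune subsets". Sections 1.2.3 and 3.8 describe the same kind of measurement for T cells, dendritic cells and myeloid suppressor cells, and section 3.9 adds plasma vesicle miRNA profiling. The protocol gives no threshold, grouping or category for any of these.

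**Tissue.** Section 9.4 says that the correlation between SUV and "the categorical variables tissue PD-1 and PD-L1 IHC will be assessed with the ANOVA test". Section 6.2 sets the unit: this relation "will be assessed for each tumor lesion". Section 7.16 samples both the primary tumor and affected lymph nodes. Section 3.4 allows up to two further biopsies "in case the PET scan shows heterogeneous and/or discrepant uptake between tumor lesions of the same patient". No patient effect is mentioned.

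**Size and status.** In section 4.3, "a sample size of 15 evaluable patients has been chosen". The same section says: "The objective of this study is descriptive and hypothesis generating", "so no formal statistical justification for the sample size is provided". No significance level is set.

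**The concern.** Each named test fits poorly with the data that the protocol says it will collect.

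A t-test of SUV across a blood variable needs two groups. A cell-subset frequency or a miRNA level does not come in two groups, so someone must choose a cut. The protocol does not say which. A cut discards information, which is costly with 15 patients, and a cut left open can be chosen after the data are seen.

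An ordinary ANOVA treats each observation as independent. If lesions are the observations and one patient supplies several, two lesions of that patient may resemble each other in SUV and in IHC class. The test then counts more independent information than exists.

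At stake is the reliability of the hypotheses that the study generates. Section 1.1.2 says that it looks for biomarkers which could be evaluated in a larger randomised trial.

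**Working it through.** The plan gives no power, significance level or effect size, so there is no stated figure to reproduce. The checks below are simulations.

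**Inputs from the protocol:** 15 patients (4.3); t-test for blood and ANOVA for IHC (9.4); lesion as unit (6.2); several tissue sites per patient (7.16, 3.4).

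**Assumptions, because the protocol is silent:** two-sided 0.05; marker and log SUV bivariate normal; 2–4 lesions per patient; SUV intraclass correlation (ICC) 0.5–0.7; three equally frequent IHC classes; within-patient correlation of the scale underlying IHC class from 0 to 1.

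**1. Cost of splitting a blood marker.** In large samples a median split keeps 2/π = 0.64 of the information, so 15 patients count as 15 × 0.64 ≈ 9.5. Simulated power at n = 15 (20,000 runs; raw-SUV column from separate runs):

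| True r | Spearman | Median-split t-test, log SUV | 11:4 split, log SUV | Median-split t-test, raw SUV |
|---|---|---|---|---|
| 0.5 | 43.7% | 31.6% | 26.4% | about 25% |
| 0.6 | 62.0% | 44.9% | 38.1% | about 37% |
| 0.7 | 80.5% | 62.2% | 52.4% | about 53% |

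Repeat runs differ by about one percentage point. The loss from splitting alone is 43.7 − 31.6 = 12, 62.0 − 44.9 = 17 and 80.5 − 62.2 = 18 points.

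The raw-SUV column assumes lognormal SUV with log SD 0.75. The only support is section 1.1.4, which gives 3.4 (±2.9) and 7.1 (±6.0). If ± is an SD, the ratios are 2.9/3.4 = 0.85 and 6.0/7.1 = 0.85, and the log SD is √ln(1 + 0.85²) ≈ 0.74. The further loss of about 7–9 points in that column comes from assumed skew, not from splitting.

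**2. ANOVA error rate when lesions cluster.** If all lesions of a patient share one IHC class, the variance of a class mean is inflated by 1 + (m − 1) × ICC, where m is lesions per patient. With m = 3 and ICC 0.5 this is 1 + 2 × 0.5 = 2.0, so 45 lesions carry the information of 22.5. If IHC class does not cluster, there is no inflation. Simulated rejection rate under no association (nominal 0.05, 15 patients):

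| Lesions per patient | SUV ICC | IHC corr. 0 | 0.5 | 0.8 | 1.0 |
|---|---|---|---|---|---|
| 2 | 0.5 | 0.049 | 0.072 | 0.094 | 0.144 |
| 2 | 0.7 | 0.049 | 0.081 | 0.106 | 0.188 |
| 3 | 0.5 | 0.052 | 0.088 | 0.130 | 0.247 |
| 3 | 0.7 | 0.049 | 0.110 | 0.173 | 0.325 |
| 4 | 0.5 | 0.052 | 0.110 | 0.176 | 0.322 |
| 4 | 0.7 | 0.051 | 0.141 | 0.227 | 0.409 |

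At IHC correlation 0.7 the rates are 0.115 and 0.135 with three lesions, and 0.151 and 0.192 with four (SUV ICC 0.5 and 0.7). For IHC correlation 0.5–0.7 the range is therefore about 6–19%. The low end is two lesions with SUV left raw and lognormal; on log SUV it is 7%.

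**3. Cases that weaken or reverse the effect.** If every lesion of a patient falls in a different IHC class, the rate at SUV ICC 0.5 drops to 0.020 (two lesions) or 0.004 (three). With uneven counts (8 patients with one lesion, 4 with two, 3 with four: 8 + 8 + 12 = 28 lesions) and SUV ICC 0.5, it is 0.051, 0.074, 0.107 and 0.182 at IHC correlation 0, 0.5, 0.8 and 1.0. With one lesion per patient it is 0.05.

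**The case against.** The case against is weak on blood and stronger on tissue.

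- **Independence is inferred.** Section 9.4 names an ANOVA without saying that lesions are pooled as independent units. A statistical analysis plan, which was not available, could add a patient term. This stands as a limit on the claim. It does not remove it: the protocol fixes both the test and the lesion as unit, and the test named has no patient term.
- **Inflation is conditional.** A reader might infer that the ANOVA will produce false SUV–IHC associations. The documents do not support that. Both SUV and IHC class must cluster within patient, and no lesion count or ICC is given. Section 2.1 expects differences between lesions of one patient, and section 3.4 seeks discordant lesions. Both weaken the inflation and could reverse it.
- **Skewness.** A reader might take the section 1.1.4 figures as proof that SUV is too skewed for these tests. They come from a cited study of 7 lung cancer patients, and ± is not labelled. Under the lognormal assumption the raw-scale t-test has a type I error of 0.039, so skew costs power but creates no excess of false positives.
- **Selection by PET-triggered biopsies.** A reader might infer a bias here. The protocol does not say that these biopsies enter the ANOVA, the trigger also includes disagreement between tracers (7.16), and no bias was calculated. This supports a sensitivity analysis, no more.
- **Exploratory status.** These are secondary analyses in a study called descriptive, and section 1.2.4 concedes for genomic profiling that strong associations cannot be identified. This limits the consequence, but does not justify labelling a continuous marker categorical.

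**Conclusion.** The blood-marker point holds on the text. Variables measured on a continuous scale are called categorical, no cut-off exists, and the named test needs one. A median split costs about 12–18 percentage points of power against Spearman for true correlations of 0.5–0.7 at n = 15, assuming two-sided 0.05 and log SUV. A less even split costs more.

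The tissue point holds conditionally. A plain ANOVA on lesions gives invalid p-values if SUV and IHC class both cluster within patient. The error is most likely too high: with 2–4 lesions per patient and SUV ICC 0.5–0.7, about 5% without IHC clustering, 6–19% at IHC correlation 0.5–0.7, and 14–41% if all lesions of a patient share a class. It falls below 5% if a patient's lesions fall in different classes. All these lesion counts and correlations are assumptions.

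Two stronger conclusions are not supported. The study sets no significance level, so no controlled error rate is lost. And nothing says that these correlations decide the content of a later trial; section 1.1.2 speaks only of biomarkers that could be evaluated there. The harm is lost power and misleading p-values.

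**What to change.** Change section 9.4 as follows.

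- **Blood markers:** keep them continuous, with one value per patient, and report Spearman correlation with SUV and its confidence interval. If a marker is to be grouped, state the cut-off before the data are seen.
- **Tissue:** model log SUV on the PD-L1 or PD-1 score with a random patient effect, or use one lesion per patient chosen by a rule set in advance. Report the result with and without the PET-triggered biopsies. The error rate of the mixed model with 15 patients was not simulated; one lesion per patient is the simpler safeguard, with a simulated ANOVA error rate of 0.05.

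The cost is about two sentences of protocol text and no new data. The drawback is wider intervals for the lesion-level results, which reflect the real number of independent patients.

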# ETHICAL CONSIDERATIONS

## Regulation statement

The study will be conducted according to the principles of the Declaration of Helsinki (amended by the 64^th^ WMA General Assembly, Fortaleza, Brazil, October 2013) and in accordance with the Medical Research Involving Human Subjects Act (WMO).

